### Outcomes

The main objective outcome measure is the WM index from WAIS-IV, and the main subjective outcome is the self- and informant-reported WM subscale from the Behavior Rating Inventory of Executive Function–Adult version (BRIEF-A) [50]. Secondary objective outcome measures include neuropsychological tests measuring (1) processing speed (Trail Making Test Part A (TMTA)), Color Word Interference Test (CWIT) parts 1 and 2 from Delis-Kaplan Executive Function System (D-KEFS), and Digit Symbol Test from Wechsler Adult Intelligence Scale 4th Edition (WAIS-IV) [51], (2) executive functions (CWIT parts 3 and 4 from D-KEFS [52] and Trail Making Part B (TMT B)), and (3) learning capacity and memory (California Verbal Learning Test (CVLT-II)). Secondary subjective outcomes include the following: (1) emotional distress (The Hopkins Symptom Checklist (HSCL)) [53], (2) quality of life (QOLIBRI) [54], (3) community integration (Patient Competency Rating Scale (PCRS) [55], and (4) everyday participation (The Participation Assessment with Recombined Tools-Objective (Part-O)). Changes in self-efficacy will be measures with the Traumatic Brain Injury Self-Efficacy Questionnaire (TBI-SE) [56] and the Memory Self-Efficacy Questionnaire (MSEQ) [57]. All measures will be applied at all three time-points (Table 1).

**Table 1 Tab1:** Overview over measures included at baseline and outcome assessments

			Baseline (T1)	Follow-up, 5 weeks (T2)	Follow-up 25 weeks (T3)
1a. Main objective outcome measure					
	*Working memory*	WAIS-IV Working Memory Index (digit span, letter-number sequencing, and mental arithmetic)	X	X	X
1b. Main subjective outcome measure					
	*Working memory*	Self and informant rating of the working memory scale in BRIEF-A	X	X	X
2a. Secondary objective outcome measures					
2b.	Secondary subjective outcome measures	Trail making A+B, D-KEFS CWIT 1-4, CVLT-II, WAIS-IV coding	X	X	X
	*Emotional distress*	The Hopkins Symptom Checklist (HSCL-25)	X	X	X
	*Activities of daily living*	Patient Competency Rating Scale (PCRS)	X	X	X
	*Quality of life*	Quality of Life after Brain Injury (QOLIBRI)	X	X	X
	*Community integration*	Participation Assessment with Recombined Tools-Objective (PART-O)	X	X	X
3. *Self-efficacy*					
		The TBI Self-Efficacy Questionnaire (TBI-SE) and Memory Self-Efficacy Questionnaire (MSEQ)	X	X	X

### Participant timeline

A study flowchart is provided in Fig. 2.

**Fig. 2 Fig2:**
[figure not shown]
Trial design

### Sample size and power calculations

Although Lindeløv et al. [4] found large treatment effects, their novel and unreplicated nature causes us to design a study that will also be informative with medium effect sizes. We set a sample size so that we can detect clinically meaningful changes of 0.5 SD on the primary outcome measures, i.e., the WAIS-IV Working Memory Index and BRIEF-A Working Memory Scale. Computed in G*Power, the group × time within-between interaction effect would require 22 completers in each group for a medium-sized effect (*ηp*^2^ = 0.07), 1% significance level (due to corrections for multiple testing), and a power of 90%. Allowing for a 20–25% drop-out rate brings the required sample to 30 participants per group, i.e., a total of *n* = 90. The success criterion in this study is thus defined as medium effect sizes (*ηp*^2^ = 0.07).

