If previous findings are replicated, and transfer effects documented, patients may have improved WM capacity, including everyday WM, improved activities of daily living, self-efficacy, psychological well-being, and quality of life. These factors are critical to independence and may in turn affect the need for community support, community integration, and return to work. The intervention is manual based and short (four sessions) and is conducted in an outpatient clinic. Hypnotic interventions are typically brief, cost-effective, suitable for both in- and outpatients, for adolescents and adults, and can be learned easily; suggestions can be administered either by another person (hetero-hypnosis) or self-administered (self-hypnosis), adding portability to the mix of benefits. As the study that is being replicated is the only one to test hypnosis in rehabilitation of WM, a lack of replication, i.e., null findings, would also be highly informative to the field. Regardless of outcome, this study can provide valuable insights to other research groups and inform future studies. Study findings may inform future studies exploring the use of clinical hypnosis in other areas of rehabilitation, such as mild TBI (i.e., post-concussion symptoms), and in other neurological conditions where WM deficit is prominent, such as multiple sclerosis and Parkinson’s disease. A next step could also be to explore potential effects beyond the domain of WM, as studies have shown that self-efficacy is associated with mental health [27], quality of life [26], functional independence [28], and community integration [29]. This study thus has the potential to influence how we understand the clinical significance of psychological factors, like self-efficacy, on functioning after ABI. If successful, our ambition is to provide recommendations and materials to implement hypnotic suggestion as an adjunct treatment following ABI in Norwegian rehabilitation clinics.

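### The sample-size section presents 0.5 SD and ηp² = 0.07 as one target, but at the settings found to give 22 per group ηp² = 0.07 is about 1.2 SD; power for 0.5 SD approaches 90% only if repeated measures correlate at about 0.9

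*Protocol article*

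**What the plan says.** The Protocol article, Sample size and power calculations, opens with a wish to be informative at medium effects and then states the aim: "We set a sample size so that we can detect clinically meaningful changes of 0.5 SD on the primary outcome measures". These measures are the WAIS-IV Working Memory Index and the BRIEF-A Working Memory Scale. The next sentence gives the only supporting calculation: "Computed in G*Power, the group × time within-between interaction effect would require 22 completers in each group", for a medium effect of ηp² = 0.07, with "1% significance level (due to corrections for multiple testing), and a power of 90" per cent. Dropout of 20–25% takes this to 30 per group and 90 in total. The section closes by making ηp² = 0.07 the success criterion.

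Trial design specifies three arms (1:1:1) and three assessments. Statistical methods plans linear mixed models on all randomised participants, 95% confidence intervals, and between-group changes from T1 to T3. The Discussion adds that "a lack of replication, i.e., null findings, would also be highly informative to the field".

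**The concern.** Since no other calculation is given, a reader takes ηp² = 0.07 to be the translation of 0.5 SD, and takes the design to have 90% power for 0.5 SD. In a repeated-measures interaction, however, what ηp² means in SD units depends on the scale the software uses and, on one of those scales, on the correlation between assessments. The section states neither, and gives no conversion.

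If ηp² = 0.07 is much larger than 0.5 SD, the trial is sized for a bigger effect than the one it calls clinically meaningful. A true 0.5 SD benefit could then easily be missed, and the miss could be read as evidence of no worthwhile effect.

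**Working it through.** **Inputs from the article.** Three arms (k = 3), three assessments (m = 3; m = 2 also tried), 22 completers per group (N = 66), alpha 0.01, power 0.90, ηp² = 0.07. So f² = 0.07/0.93 = 0.0753 and f = 0.274.

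**Assumed, because not stated.** Correlation ρ between repeated measures, equal across time points; SD equal at each assessment.

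**1. Reproducing 22 on G*Power's default scale.** Noncentrality λ = f²·N·m/(1−ρ), df1 = (k−1)(m−1), df2 = (N−k)(m−1).
- 3 × 2, ρ = 0.5, f rounded to 0.27: λ = 0.0729·66·2/0.5 = 19.2, df 2 and 63. Power is 0.91 at 22 per group and 0.89 at 21, so 22 is the minimum. (Unrounded f gives 21.)
- 3 × 3, ρ = 0.32: λ = 0.0753·66·3/0.68 = 21.9, df 4 and 126. Power is 0.90 at 22 and 0.88 at 21, so again 22.
- 3 × 3, ρ = 0.5, nonsphericity ε = 0.7: also 22.
- 3 × 3, ρ = 0.5, ε = 1: 17.

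The dropout step also reproduces: 22/0.75 = 29.3, rounded up to 30.

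**2. What ηp² = 0.07 means on that scale.** f² is the mean squared interaction cell effect divided by the squared SD. Let one arm change d SD more than the other two.
- Two times: f² = d²·(2/9)·(1/4) = d²/18, so f = 0.236·d. Then f = 0.274 gives d = 1.16 SD.
- Three times, difference present at T2 and T3: f² = d²·(2/9)·(2/9) = 4d²/81, so f = 0.222·d. Then f = 0.274 gives d = 1.23 SD.
- In reverse, d = 0.5 gives f = 0.118 or 0.111, i.e. ηp² = f²/(1+f²) = 0.014 or 0.012.

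Other patterns of arm means give 1.10 to 1.43 SD. None comes near 0.5.

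**3. The 'as in SPSS' scale.** Here λ = f²·(N−k)(m−1), and ρ drops out.
- Two times: d = 3f·√(1−ρ) = 0.823·√(1−ρ), which is 0.58 SD at ρ = 0.5 and 0.50 SD at ρ = 0.63. The two effect sizes can agree.
- But with N = 66, λ = 0.0753·63 = 4.74 (two times) or 9.48 (three times), giving power of 23% or 43%. Reaching 90% would take 80 or 49 per group.

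**4. Power for a true 0.5 SD with 22 per arm at 1%.** For the 3 × 3 interaction λ = 0.01235·66·3/(1−ρ) = 2.44/(1−ρ). For hypnosis versus active control, the difference in change has SE = √(2(1−ρ)·2/22), in SD units, with 42 df. The difference detectable with 90% power is about (2.698 + 1.302)·SE = 4.00·SE.

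| ρ | 3 × 3 interaction | Hypnosis vs active control | SE | Detectable at 90% power |
|---|---|---|---|---|
| 0.32 | 11% | – | – | – |
| 0.5 | 17% | 16% | 0.302 | 1.21 SD |
| 0.7 | 35% | 30% | 0.234 | 0.93 SD |
| 0.8 | 58% | 48% | 0.191 | 0.76 SD |
| 0.9 | 94% | 84% | 0.135 | 0.54 SD |

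At the settings in step 1 that give 22, power for 0.5 SD is 11–17%. The interaction reaches 90% only at ρ of about 0.89 (3 × 3) or 0.90 (3 × 2).

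**The case against.** **The article never writes that power is 90% for 0.5 SD.** This is correct. It attaches 90% to ηp² = 0.07 and gives 0.5 SD as a design aim. But the one calculation is offered in support of that aim, so the inference is the natural one and the section does nothing to prevent it.

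**Everything turns on a correlation that the article does not give.** This stands, and is why a range is shown. The article offers no retest correlation for either outcome, so no single value can be called the right one, and at ρ near 0.9 the aim would be met. However, 0.9 is not a value that produces 22 from ηp² = 0.07 on the default scale. If 0.5 SD meant the SD of the change score, the 3 × 2 power would be about 16% whatever ρ is.

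**The mixed model uses all randomised participants, so 22 is a floor.** This is partly right. With all 30 per arm retained, 3 × 3 power for 0.5 SD rises to 27% at ρ = 0.5 and 53% at ρ = 0.7, still well short of 90%.

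**A reader might infer that 22 was computed for the wrong design.** The article does not support that. The 3 × 3 design gives 22 at ρ of about 0.32, or at ρ = 0.5 with ε = 0.7, and neither ρ nor ε is stated.

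**A reader might also infer that a null result could never exclude 0.5 SD.** That goes too far. The article plans 95% intervals. With 22 per arm the half-width is 2.018·SE: 0.61, 0.47, 0.39 and 0.27 SD at ρ = 0.5, 0.7, 0.8 and 0.9. An estimate near zero would exclude 0.5 SD at ρ = 0.7 or above, but not at 0.5. At the 99% level (2.698·SE) the half-width is 0.63 SD at ρ = 0.7. The Discussion's remark, moreover, is about failing to replicate an earlier, large effect, and for effects of about 1.2 SD the design has roughly 90% power even at ρ = 0.5.

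**Conclusion.** The point holds. The number 22 is arithmetically sound for ηp² = 0.07 on G*Power's default scale, but that input is about 1.16–1.23 SD, more than twice the stated 0.5 SD. On the scale where ηp² = 0.07 can be near 0.5 SD, 22 per group gives 23–43% power. Neither scale yields 0.5 SD, 22 per group and 90% power from ηp² = 0.07.

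Taken directly, power for 0.5 SD with 22 completers per arm at 1% runs from 17% (ρ = 0.5) to 94% (ρ = 0.9) for the interaction, and from 16% to 84% for hypnosis versus active control. These figures assume equal SDs, equal correlations and, for the interaction, one arm differing from the other two by the same amount at T2 and T3. They do not show that the trial is underpowered at its true correlation, which is unknown here. They show that the stated detectable effect is not the one the calculation supports.

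**What to change.** Keep n = 90 and rewrite the sample-size paragraph:

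- State the assumed correlation and its basis, the number of measurements entered, and the G*Power effect-size option.
- Replace the implied 90% power for 0.5 SD with the difference between hypnosis and active control that 22 completers per arm can detect with 90% power at 1% (about 1.21, 0.93, 0.76 and 0.54 SD at correlations 0.5, 0.7, 0.8 and 0.9), and give the power at 0.5 SD (16%, 30%, 48% and 84%).
- Restate the ηp² = 0.07 success criterion on the same scale, so that it is clear what difference in SD would count as success.
- In the Discussion, separate failure to replicate the earlier large effect from evidence against a 0.5 SD effect. Claim the latter only if the planned confidence interval for hypnosis minus active control excludes 0.5 SD.

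The cost is one paragraph and one sentence of interpretation. No patients, assessments or analyses are added. The stated power becomes less favourable.

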### Randomization and blinding

Eligible patients will be identified by the study PI (author [name]) from the department of cognitive rehabilitation (KReSS) at Sunnaas Rehabilitation Hospital. After baseline assessment, participants will be randomly allocated to either of the three groups. The randomization sequence will be generated electronically in STATA by an independent statistician.

The allocation sequence will be stored in a database that can only be accessed by the study’s principal investigator. It will not be possible to blind neither the participants nor the PhD candidate who will conduct the hypnotic suggestions. Outcome assessments will, however, be blinded in that a person external to the study will perform these without knowledge of group allocation. Our research group has extensive experience in managing blinded clinical trials, and we are confident that this can be conducted in a truly blinded way without contamination. Data analysis will also be blinded in that fake ID numbers will be assigned to participants in the final database, ensuring that the statistical analysis is performed without knowledge of true group content until after the analyses are finalized.

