## Methods

### Trial design

The study is organized as a randomized controlled superiority trial with parallel group design and three arms including (1) an intervention group, (2) an active control group, and (3) a passive control group. Participants will be randomly allocated in a 1:1:1 ratio to either of the three groups. The intervention group will receive four weekly 1-h sessions with hypnosis treatment (induction + hypnotic suggestion), while the active control group will receive four weekly 1-h sessions of non-targeted hypnotic suggestions (induction + mindfulness-based instructions) to factor out nonspecific treatment effects. The passive control group will be assessed at the same time points as the other two groups to isolate retest effects. Each participant will be assessed three times: (1) at baseline (T1), (2) immediately after the intervention which is 5 weeks post baseline (T2), and (3) 25 weeks after baseline (T3, follow-up). The study will follow the CONSORT statement facilitating complete and transparent reporting and aiding critical appraisal and interpretation (http://www.consort-statement.org/). This study expands the design of Lindeløv et al.’s study through a larger number of participants, the inclusion of far-transfer outcome measures, and the exploration of potential underlying mechanisms of treatment effects. Because this study is performed in collaboration with the principal investigator of the original study [4], we rely on learnings from that study rather than conducting a small-scale pre-study pilot and/or feasibility trial. The intervention will be based on the hypnosis scripts by Lindeløv et al. translated from Danish to Norwegian [4].

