### Study setting and participants

Eligible participants are recruited at the department of cognitive rehabilitation at Sunnaas Rehabilitation Hospital ([name]). The department discharge approximately 370 patients a year making it realistic to reach the target sample size. Assessments and interventions will be conducted at the outpatient clinic at the Sunnaas Rehabilitation Hospital. The therapist will collect signed written informed consent forms before baseline assessments.

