### Eligibility criteria (10)

#### Inclusion and exclusion criteria

Inclusion criteria are a documented nonprogressive ABI, minimum 12-month post-injury, ongoing WM deficits (by self-report and/or neuropsychological assessment), and age between 18 and 67 years. Exclusion criteria are severe mental illness (e.g., diagnosed major depressive disorder, schizophrenia, or bipolar disorder), progressive neurologic disease, and/or ongoing ICD-10 diagnosis of substance use disorder or lack of Norwegian language skills. Participants will be discouraged from participating in intensive in-patient cognitive rehabilitation while included in the trial but will not ask them to refrain from ordinary long-term community-based treatment such as physiotherapy and/or occupational therapy. Service provision during the trial will be documented.

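### Concealment of allocation from the recruiting principal investigator is not secured, because the same role identifies eligible patients and has sole access to the stored sequence

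*Protocol article*

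**What the plan says.** All of this comes from the protocol article.

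- **Recruitment** (Randomization and blinding): "Eligible patients will be identified by the study PI", from one department of one hospital.
- **Making the sequence** (same section): "The randomization sequence will be generated electronically in STATA by an independent statistician".
- **Keeping the sequence** (same section): "The allocation sequence will be stored in a database that can only be accessed by the study’s principal investigator".
- **Timing** (same section): "After baseline assessment, participants will be randomly allocated to either of the three groups". The ratio is 1:1:1 (Trial design).
- **Consent** (Study setting and participants): "The therapist will collect signed written informed consent forms before baseline assessments".
- **Eligibility** (Inclusion and exclusion criteria): one criterion is "ongoing WM deficits (by self-report and/or neuropsychological assessment"), so self-report alone can satisfy it. The other criteria are firmer: documented nonprogressive injury, at least 12 months since injury, an age range and listed exclusions.
- **Blinding** (Randomization and blinding): participants and the person giving the sessions cannot be blinded. For outcome assessment, "a person external to the study will perform these without knowledge of group allocation". The analysis is also to be done blind to group.

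The article describes no release procedure: no third party who gives out assignments, no sealed envelopes, and no disclosure of one assignment at a time after enrolment.

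**The concern.** Allocation concealment means that whoever decides which patient enters, and when, cannot know the arm that patient will receive. Here the article gives recruitment and access to the sequence to the same role. If upcoming assignments can be read, a patient thought likely to respond could be put forward when a hypnosis slot is next, and another patient held back.

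Such selection acts before randomisation, so later safeguards do not undo it. It matters more than usual in this trial. Participants and therapist know the arm, and one main outcome is self- and informant-rated, so concealment is one of the few remaining protections. The trial also sets out to test a surprisingly large earlier result under a rigorous design, and its Background criticises previous hypnosis studies for weaknesses that include randomization. A positive result would be open to similar criticism.

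**Working it through.** The article gives no figure to reproduce. The check sets the statements about roles side by side and asks whether any safeguard separates recruitment from knowledge of the sequence.

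**1. Is it the same role?** Randomization and blinding uses the singular for both tasks: the study PI identifies patients, and the study's principal investigator has access. Data Availability mentions principal investigators in the plural, but only about cleaned data sets. It gives no ground for reading two different people into the randomisation section. The therapist is a separate person, since Dropout and data retention names the PI and the therapist as alternatives.

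**2. Does any stated safeguard keep upcoming assignments from the PI?**

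| Stated safeguard | What it protects | Does it conceal the sequence from the recruiter? |
|---|---|---|
| Independent statistician generates the sequence | How the list is made | No; the list is then stored where only the PI has access |
| Allocation after baseline assessment | T1 scores are obtained before the arm is assigned | Not if the list can be read beforehand |
| Consent taken by the therapist, who has no stated access | The consent conversation | Partly; whom to put forward, and when, stays with the PI |
| External assessor without knowledge of group | Outcome measurement | No |
| Blinded analysis | Analysis choices | No |
| Intention-to-treat | Keeps the groups as allocated | No; it also keeps any bias in how they were formed |
| Group main effect in the mixed model | Baseline differences in the outcome | No; differences in motivation, suggestibility or expected improvement would act on the time-by-treatment term, which carries the effect |

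**3. Is there room for selection?** Study setting and participants gives about 370 discharges a year. Trial status gives recruitment from October 2022 to an estimated June/July 2024, which is 20 to 21 months:

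- 370 × 20/12 ≈ 617 discharges
- 370 × 21/12 ≈ 648 discharges

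That compares with 90 places. The fraction of those patients who are eligible is not stated and could be small, so this only indicates that one person chooses from a larger pool. Within that pool, the working memory criterion leaves some judgement.

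**4. How far does the exposure reach?** The statistician has also seen the sequence, so sole access refers to the database after generation. The exposure lies in identification, ordering and timing. It does not extend to consent or outcome assessment.

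**The case against.** The strongest reply is that the article says only where the sequence is stored and who may open the database. It does not say that the whole list can be read in advance, or how each assignment is released. A journal article often leaves that to the full protocol, and assignments may in practice be locked until enrolment. Between identification and allocation there also come the patient's own decision, consent by someone else and a full T1 assessment. To steer, the PI would have to predict which patient reaches which position in the sequence. Most eligibility criteria leave little discretion.

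Much of this stands, and it limits what can be claimed. A reader might infer that allocation is in fact unconcealed, that the PI does see the next arm before approaching a patient, or that the results are biased by some amount. The document supports none of these. Putting a number on the bias would need an assumed share of steered patients and an assumed difference in their prognosis, and the article gives neither.

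The role conflict itself is not answered. It is not a detail left out: the article states who recruits and who has access, and the two statements name the same role. If assignments are in fact withheld from the PI, the section is misleading as it reads and needs correcting for that reason.

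**Conclusion.** The point holds in this form: followed as written, the plan does not secure concealment from the person who identifies patients, so selection bias is possible. It should be fixed before any further patient is allocated, because analysis cannot repair it afterwards and it bears on every comparison between arms.

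Its size cannot be estimated from the document. The conclusion does not depend on sample size, power, significance level or dropout. It rests on two readings: that both mentions of the principal investigator mean the same person, and that no unshown procedure withholds upcoming assignments. If the second is wrong, the remedy shrinks to correcting the text.

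The protocol version is dated December 2023 and recruitment began in October 2022. Allocations made in the meantime took place under the described arrangement and can only be disclosed.

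**What to change.** 1. Have the independent statistician, or another person with no role in identifying, enrolling or treating patients, regenerate the unused part of the sequence and hold it without PI access. Moving the existing list is not enough, because the PI may already have read it.
2. Release each assignment singly, only after that patient's eligibility, consent and T1 data are recorded.
3. Amend Randomization and blinding to say who holds the sequence and how an assignment is released.
4. Log the date of the changeover. Report as a limitation that earlier allocations were made while the PI had access to the sequence. A comparison of baseline data before and after that date would not settle the matter: there are only 30 patients per arm in total, and it cannot show differences in unmeasured traits.

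**Cost.** The statistician is already part of the trial, so the work is one regeneration, a change of access rights and a short amendment. Each assignment must then be requested by message. Earlier allocations cannot be repaired. If enrolment has already closed, only the corrected description and the stated limitation remain.

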**Methods:**

Ninety patients will be recruited from the Sunnaas Rehabilitation Hospital. Inclusion criteria are nonprogressive ABI, minimum 12-month post-injury, ongoing WM deficits, and age between 18 and 67 years. Patients will be randomized to either (a) an intervention group receiving four weekly 1-h sessions with induction and hypnosis, (b) an active control group receiving four weekly 1-h sessions of induction and mindfulness, or (c) a passive control group without intervention. The targeted procedure consists of suggestions about enhancing WM functions, for example through the instantiation of preinjury WM capacity in the present using age regression or through visualizations of brain plasticity. The non-targeted suggestions contain no explicit mention of ABI- or WM-related abilities. Each participant will be assessed at baseline, immediately after intervention, and 6 months after baseline. The primary outcome is the WM index from WAIS-IV and self- and informant-reported WM subscale from BRIEF-A, a questionnaire exploring executive functioning in everyday life. Secondary outcomes include a cognitive composite score derived from tests measuring processing speed, executive functions, learning capacity and memory, and self-reported measures of emotional distress, quality of life, and community integration. Exploratory measures include self-rated ABI and WM-related self-efficacy.

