### Interventions

The treatment protocol is identical to the study that is being replicated. During the first phase of the study, the treatment group and the active control group will receive identical procedures, including welcoming, hypnotic inductions, hypnotic re-alerting, and farewell. The groups differ in between the hypnotic induction and hypnotic re-alerting. The targeted procedure consists of suggestions about enhancing WM functions through the instantiation of preinjury WM ability in the present using age regression and visualizations of brain plasticity. The non-targeted suggestions contain no explicit mention of brain injury or WM-related abilities and thus serve as an active control, i.e., to isolate the ‘targetedness’ of suggestion as the independent variable by factoring out other influences from placebo, retest effects, etc. These non-targeted suggestions are borrowed from mindfulness meditation practices, involving body and thought awareness as they have demonstrated no or small effects on cognitive abilities in participants with ABI [48, 49]. All sessions will last for about 1 h, and the patients are invited to either sit in a comfortable chair or lay down on a bench during the procedures. We have access to the full treatment manual used by Lindeløv et al. in Danish. The manual has been translated into Norwegian. Throughout the spring of 2021, we tested the manual with the active treatment condition with two user representatives at Sunnaas Rehabilitation Hospital. This has given us the opportunity for closer collaboration with users regarding feasibility and adherence to intervention protocol.

To secure compliance to the protocol, regular supervision is provided to the therapist conducting the intervention. There are few side effects of hypnosis, and most people report well-being after hypnotic intervention. Participants are informed about the harmless nature of hypnosis, but also that if they wish to end the session for any reason, treatment will be immediately aborted. The therapist registers any occurrence of uncomfortableness or adverse effects of the treatment. Participants will further be informed that this is an experimental study with unknown effects. Participation is not time-consuming and will not be at the expense of other treatment.

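### The blinded-assessment statement does not hold for self-reported BRIEF-A, and the three-arm success criterion lets a difference from the untreated arm count as a finding on it

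*Protocol article*

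**What the plan says.** All references are to the protocol article.

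- **Blinding.** Randomization and blinding first concedes that "It will not be possible to blind neither the participants nor the PhD candidate who will conduct the hypnotic suggestions". The next sentence states that "Outcome assessments will, however, be blinded in that a person external to the study will perform these without knowledge of group allocation". No exception is made for questionnaires.
- **Primary outcomes.** Outcomes names the WAIS-IV Working Memory Index as the main objective measure, and says that "the main subjective outcome is the self- and informant-reported WM subscale" of BRIEF-A. Sample size and power calculations treats both as primary, with the aim to "detect clinically meaningful changes of 0.5 SD on the primary outcome measures".
- **Roles of the control arms.** Interventions says that the active control isolates the targeted nature of the suggestions "by factoring out other influences from placebo, retest effects, etc". The Abstract describes "a passive control group without intervention", and Trial design gives that arm one role, isolating retest effects.
- **Test and criterion.** Sample size and power calculations uses a group × time interaction (partial eta squared 0.07, alpha 1%, power 90%, 22 completers per group, 90 randomized in total). It sets the success criterion at that effect size for the primary measures together.
- **Contrast.** Statistical methods plans between-group changes without naming the pair of arms, and promises that the analytic strategy will be preregistered.

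**The concern.** An external tester removes observer bias only where the tester produces the score. For a self-report scale the patient produces it, and every patient knows whether he or she attended four sessions or none. The unqualified sentence therefore credits a primary outcome with a protection that it does not have.

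This matters because of how the arms enter the test. An interaction over three arms does not distinguish targeted hypnosis differing from the active control from both session arms differing from no treatment. The second pattern is what expectancy would produce on a self-rating. It says nothing about the targeted suggestion, yet it could meet the success criterion. Everyday working memory is also the main addition over the replicated trial, which the Background faults for having no such measure. The BRIEF-A result will therefore carry much of the new claim.

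**Working it through.** **1. The plan's own figure.** For a within-between interaction with k groups, m time points, N completers and correlation ρ:

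λ = f²·N·m/(1−ρ), df1 = (k−1)(m−1), df2 = (N−k)(m−1), with f² = 0.07/0.93 = 0.0753 (f = 0.274).

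The article gives neither ρ nor m, so both are assumed. At alpha 0.01 and 90% power:

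| Groups × times | ρ | Needed per arm | Power at 22 per arm |
|---|---|---|---|
| 3 × 2 | 0.5 | 21 | 91.9% |
| 3 × 3 | 0.5 | 17 | 97.8% |
| 3 × 3 | 0.3 | 23 | 89.0% |

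The stated 22 lies within this range. With 25% dropout, 22/0.75 = 29.3, so 30 per arm. The figure is reproducible to within a patient or two, and the point does not depend on it.

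**2. Who produces each score.**

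| Measure | Score produced by | Blinding per the article |
|---|---|---|
| WAIS-IV index and other neuropsychological tests | External tester | Blinded |
| BRIEF-A, self | Patient | Patient not blinded |
| BRIEF-A, informant | Informant | Not stated |

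**3. Expectancy alone.** Assume no true effect and a reporting shift of b SD at T2 and T3 in both session arms, with none in the passive arm. The cell means are (0, b, b), (0, b, b) and (0, 0, 0).

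Removing row and column means leaves these interaction terms, in units of b:
- each session arm: −2/9, 1/9, 1/9
- passive arm: 4/9, −2/9, −2/9

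The squares sum to 2 × 6/81 + 24/81 = 36/81 = 4/9. With n = 22 per arm:

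λ = n·(4/9)·b²/(1−ρ), df1 = 4, df2 = 63 × 2 = 126.

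Example: b = 0.5 and ρ = 0.5 give λ = 22 × 0.444 × 0.25/0.5 = 4.89.

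For the pairwise contrast in T1-to-T2 change, the SD of change is √(2(1−ρ)) and the noncentrality is b/[√(2(1−ρ))·√(2/22)] on 42 df. At b = 0.5 and ρ = 0.5 this is 0.5/(1 × 0.3015) = 1.66.

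Probability of p < 0.01, with ρ = 0.5 / 0.7 in each cell:

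| Shift b | λ | Three-arm interaction | Hypnosis vs passive | Hypnosis vs active |
|---|---|---|---|---|
| 0.2 SD | 0.78 / 1.30 | 2.3% / 3.5% | 2.7% / 4.0% | 1% |
| 0.3 SD | 1.76 / 2.93 | 4.7% / 8.5% | 5.3% / 9.0% | 1% |
| 0.5 SD | 4.89 / 8.15 | 17.1% / 35.0% | 16.3% / 30.2% | 1% |

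The last column stays at the nominal level because an equal shift in the two session arms cancels. These rates concern significance of the interaction at the 1% level; the article words its success criterion as an effect size.

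**The case against.** The strongest reply is that nothing is hidden. The article admits that participants are unblinded, and it explains assessor blinding by reference to an external person, so a careful reader can see its scope. The design also already answers the expectancy problem: the active arm is there for nonspecific effects, the passive arm for retest, and nowhere is the passive contrast offered as a control for expectancy. The choice of confirmatory pair can be left to an analysis plan, and preregistration is promised. Finally, the article hypothesizes that hypnosis works partly through self-efficacy, so changed expectation may be part of the effect rather than pure bias.

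Much of this stands, and it limits the point. But disclosing that participants are unblinded does not make the next sentence true for a scale they fill in themselves. Nor is the criterion simply left open: the article ties it to an all-arm interaction for both primary measures, which does not respect the roles it gives the arms. If expectancy is partly mechanism, the passive comparison still cannot separate it from reporting.

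A reader might infer more than the documents support:

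- **That the informant rating is unblinded too.** The article does not say either way.
- **That the active control fails because session patients know which suggestions are experimental.** The article does not show what they are told; it says only that they learn the study is experimental with unknown effects.
- **That the analyst is unblinded because "fake ID numbers will be assigned to participants in the final database".** The same sentence goes on to say that the analysis is done without knowledge of what the groups are, so masking of arms is the stated aim.
- **That a spurious result is likely.** The size of any shift is unknown. A 0.5 SD shift equals the trial's whole target, and correlations above 0.7 move further from the stated 22 per arm (in the 3 × 3 design, 0.7 already needs only 11).

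**Conclusion.** The point holds for self-reported BRIEF-A. Blinded assessment is claimed without exception, yet this primary outcome is rated by patients whom the plan says cannot be blinded. A success criterion spanning three arms then allows a difference from the untreated arm alone to count. The tester-scored measures are not affected by this rating problem.

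Expectancy-only reporting would raise the 1% error rate of the interaction to about 2–4% at a 0.2 SD shift, 5–9% at 0.3 SD and 17–35% at 0.5 SD. This rests on an assumed shift that is equal in both session arms and present at both follow-ups, ρ of 0.5 to 0.7, three time points and 22 completers per arm. Neither the shift nor ρ can be taken from the documents. The 1% for hypnosis versus active control likewise requires equal expectations in those two arms. The matter should be corrected, but it does not undermine the design, which already contains the right comparator.

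**What to change.** 1. In the preregistered analysis, name hypnosis versus active control as the confirmatory contrast for BRIEF-A. Report comparisons with the passive arm as supportive, and describe them as reflecting treatment plus expectancy.
2. In Randomization and blinding, limit the statement on blinded outcome assessment to the performance-based tests.

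Both are wording changes and need no extra patients, visits or data. The cost is that the BRIEF-A comparison with the passive arm loses confirmatory status. The sample size was also not computed for this pairwise contrast. By the pairwise formula above, a true 0.5 SD difference in T1-to-T2 change between two arms of 22 would reach p < 0.01 in only 16–30% of trials at ρ of 0.5 to 0.7. That limit applies to any pair of arms; it should be stated alongside the contrast.
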